## Abstract

**Background and Aims:**

The past-year prevalence of problematic pornography use (PPU) was 1–6% in adult populations. As a result of treatment obstacles and barriers, such as unaffordable treatments, only a minority of problematic pornography users may seek treatment. Having a free, online, self-help program may overcome treatment barriers and may help those individuals who cannot receive traditional or offline treatment for PPU. Although the effectiveness of such online programs reducing substance use and problematic gambling have been reported, no prior study has examined the efficacy of an online self-help intervention aiming to reduce PPU.

**Methods:**

This two-armed randomized controlled trial (RCT) will examine the effectiveness of an online self-help program (Hands-off) to reduce PPU, while also considering psychopathological comorbidities. The six-week intervention condition includes six core modules developed to reduce PPU based on motivational interviewing, cognitive behavioral therapy, mindfulness, and wise social-psychological intervention techniques. The target sample size is 242 participants. Self-report questionnaires will be administered at baseline, right after the end of the intervention, at one-month, and three-month follow-ups after the end of the intervention. The primary outcome will be the level of PPU. Secondary outcomes will include pornography use frequency, pornography craving, pornography use-avoidance self-efficacy, sex mindset, sexual satisfaction, negative and positive emotions, and life satisfaction. Data will be analyzed on an intention-to-treat basis using linear mixed models.

**Results:**

Results will be reported at conferences and published in a scientific peer-reviewed journal. The participants will be sent a lay-person-friendly summary of the results via e-mail.

## Introduction

In the past decades, pornography use has started to increase among young adults—even among pre-adolescent children—presumably due to the widespread access to the Internet (Lewczuk, Wojcik, & Gola, 2019; Price, Patterson, Regnerus, & Walley, 2016). Based on findings of recent nationally-representative studies from Australia (Rissel et al., 2017) and the US (Grubbs, Kraus, & Perry, 2019), 69–76% of men and 33–41% of women used pornography in the past year. However, only 4–6% of men and 1–2% of women reported having felt addicted to pornography (Grubbs et al., 2019; Rissel et al., 2017). Although pornography use may have little or no adverse effect on most people's lives, it may become problematic for some and may result in severe adverse consequences (e.g., job loss, problems in romantic relationships (Bőthe, Tóth-Király, et al., 2018b; Bőthe, Tóth-Király, Demetrovics, & Orosz, 2017; Bőthe, Tóth-Király, Potenza, Orosz, & Demetrovics, 2020; Ford, Durtschi, & Franklin, 2012; Perry, 2019)) leading to treatment-seeking behavior among men and women as well (Bőthe, Tóth‐Király, Demetrovics, & Orosz, 2020; Gola, Lewczuk, & Skorko, 2016; Lewczuk, Szmyd, Skorko, & Gola, 2017).

Despite the inclusion of Compulsive Sexual Behavior Disorder (CSBD) in the 11th version of *International Statistical Classification of Diseases and Related Health Problems* (ICD-11) (World Health Organization, 2019), there is no official diagnosis for problematic pornography use (PPU) (Fernandez & Griffiths, 2019). However, as PPU is often considered as a manifestation of CSBD, the same diagnostic guidelines may be applied (Fernandez & Griffiths, 2019). For problematic users, pornography is the central focus of their life; they experience failures when trying to control their use with recurring unsuccessful efforts to regulate or reduce it, and they engage in pornography use despite the adverse consequences (e.g., job loss) (Bőthe, Tóth-Király et al., 2018b; World Health Organization, 2019). Besides the aforementioned potential adverse consequences, high rates of other psychological and psychiatric problems were reported concerning PPU. Mood disorders (31–72%), anxiety disorders (33–47%), substance use disorders (14–41%), and attention deficit hyperactivity disorder (ADHD) (3–67%) are reported to be comorbid and prevalent among problematic pornography users or individuals with CSBD (Blankenship & Laaser, 2004; Bőthe, Koós, Tóth-Király, Orosz, & Demetrovics, 2019; Grubbs, Volk, Exline, & Pargament, 2015; Kafka & Hennen, 2002; Kraus, Potenza, Martino, & Grant, 2015; Nelson, Padilla-Walker, & Carroll, 2010; Raymond, Coleman, & Miner, 2003; Reid, 2007; Reid, Carpenter, Gilliland, & Karim, 2011; Reid, Davtian, Lenartowicz, Torrevillas, & Fong, 2013; Scanavino et al., 2013; Wéry et al., 2016; Willoughby, Busby, & Young-Petersen, 2019; Willoughby, Carroll, Nelson, & Padilla-Walker, 2014). Nevertheless, evidence-based treatments offered for problematic pornography have remained scarce worldwide.

Based on the findings of recent literature reviews discussing the treatment approaches for PPU, problematic online sexual activities, and CSBD (Dhuffar & Griffiths, 2015; Garcia et al., 2016; Hook, Reid, Penberthy, Davis, & Jennings, 2014; Kaplan & Krueger, 2010; Naficy, Samenow, & Fong, 2013; Sniewski, Farvid, & Carter, 2018; von Franqué, Klein, & Briken, 2015; Wéry & Billieux, 2017), cognitive behavior therapy (CBT), acceptance and commitment therapy (ACT), motivational interviewing techniques, and mindfulness-based approaches may be efficient in the treatment of CSBD and PPU. However, the evidence is mostly based on case reports and uncontrolled studies (Dhuffar & Griffiths, 2015; Garcia et al., 2016; Hook et al., 2014; Kaplan & Krueger, 2010; Naficy et al., 2013; Sniewski et al., 2018; von Franqué et al., 2015; Wéry & Billieux, 2017). To the best of the authors' knowledge, only three studies examined the effectiveness of short (i.e., 12 sessions), ACT- and CBT-based interventions aiming to reduce specifically PPU (i.e., not hypersexuality, sexual addiction, or compulsive sexual behaviors), including a control group (Crosby, 2011; Crosby & Twohig, 2016; Minarcik, 2016). Each of these studies reported a significant improvement in the participants' pornography use-related symptoms and problems compared to the control group not only during the post-treatment assessments but in the follow-up assessments as well (i.e., 12–20 weeks after the end of the interventions) (Crosby, 2011; Crosby & Twohig, 2016; Minarcik, 2016). Although these studies demonstrated the efficiency of ACT- and CBT-based methods in the reduction of PPU, they only reached 12 to 28 participants presumably due to the offline settings of the interventions (i.e., individual sessions with a therapist).

Even though effective interventions exist for PPU (Crosby, 2011; Crosby & Twohig, 2016; Minarcik, 2016), there is still a significant unmet need for scalable treatment. Web-based (online) interventions may contribute to the reduction of traditional treatment barriers and may facilitate treatment utilization. Treatment barriers and obstacles include social and individual barriers as well, such as high mental health stigma, feelings of shame to talk about pornography use, or unaffordable treatment costs (Dhuffar & Griffiths, 2016). Online self-help tools may reduce both social and individual treatment barriers by being free and easy-to-use tools, providing anonymity, privacy, flexibility, short or no waiting time, and supporting participants' autonomy and self-efficacy (Baumgartner et al., 2019; Haug, Castro, Wenger, & Schaub, 2018; Herrero et al., 2019; Weisel et al., 2018). Despite the advantages mentioned above and the cost-effectiveness of online interventions,—compared to face-to-face interventions—online interventions should not be considered as replacements for face-to-face treatments but as additional tools that can provide treatment for those individuals who are not yet in treatment or hesitant to seek traditional forms of treatment. Also, it has to be noted that online interventions have some disadvantages as well, such as low treatment commitment and adherence, limited individualization options, limited treatment tailoring, and, thus, higher dropout rates (Haug et al., 2018; Schaub et al., 2016).

Currently, there is a gap in the literature with respect to evidence-based, scalable, online interventions that can effectively reduce PPU. Therefore, the aim of the present study is to test the effectiveness of a web-based self-help program (Hands-off) to reduce PPU in a two-armed randomized controlled trial (RCT), while also considering psychopathological comorbidities. The primary outcome will be the change in the level of PPU between baseline and follow-up assessments (after the end of the six-week-long intervention (t_1_), at a one-month follow-up (t_2_), and three-month follow-up (t_3_)) compared to a control condition. The secondary outcome measures will include beneficial changes in the intervention groups' pornography use frequency, pornography craving, pornography use-avoidance self-efficacy, beliefs about the malleability of sexual life, sexual satisfaction, negative and positive emotions, and life satisfaction over time compared to the control group.

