### Sample size calculation

Two groups (treatment vs. control group) will be compared over time (t_0_, t_1_, t_2_, and t_3_). Based on the results of previous PPU reduction interventions (Crosby, 2011; Crosby & Twohig, 2016; Minarcik, 2016), small effect sizes (Cohen *d* = 0.2) may be anticipated when comparing the treatment and control conditions. After calculations conducted with the G*Power software, a sample size of 121 in each study group would have 80% power to detect the difference with an alpha error of 5% and two-tailed testing. Therefore, the recruitment of a minimum of 242 participants would be sufficient to detect differences between the treatment and control groups over time.

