### Hypotheses

Concerning the primary outcome, we hypothesize that participating in the intervention condition (study arm 1)—compared to the control condition (study arm 2)—will result in lower levels of PPU comparing the baseline and the follow-up assessments. Regarding the secondary outcomes, we hypothesize that participating in the intervention condition—compared to the control condition—will result in lower levels of pornography use frequency, lower levels of pornography craving, lower levels of negative emotions in general, higher levels of sexual satisfaction, higher levels of pornography avoidance self-efficacy, higher levels of beliefs about the malleability of sexual life, higher levels of life satisfaction, and higher levels of positive emotions in general over time.

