#### Primary outcome

The primary outcome of interest will be the Problematic Pornography Consumption Scale (PPCS) (Bőthe, Tóth-Király et al., 2018b). The PPCS assesses past-six-month PPU covering six factors: salience, tolerance, mood modification, withdrawal, relapse, and conflict (Griffiths, 2005). The scale includes 18 items with three items per each factor. Respondents indicate answers on seven-point scales (1 = “never”; 7 = “all the time”). Higher scores on the scale indicate higher levels of PPU. A score of 76 (out of 126) or higher indicates a high-risk of PPU.

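### The primary outcome spans three follow-ups, but the single 5% alpha and the sample size attach to one unnamed difference, and the last follow-up falls after controls gain access

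*Protocol article*

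**What the plan says.** All references are to the protocol article.

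- **Introduction (aim).** "The primary outcome will be the change in the level of PPU between baseline and follow-up assessments", with the assessments listed as "after the end of the six-week-long intervention (t_1_), at a one-month follow-up (t_2_), and three-month follow-up (t_3"), compared with control.
- **Hypotheses.** The intervention "will result in lower levels of PPU comparing the baseline and the follow-up assessments". The follow-ups are in the plural and none is singled out.
- **Primary outcome.** "The primary outcome of interest will be the Problematic Pornography Consumption Scale (PPCS"). This fixes the instrument, which has a six-month recall period, but no visit.
- **Sample size calculation.** "small effect sizes (Cohen *d* = 0.2) may be anticipated when comparing the treatment and control conditions", and 121 per arm is said to give "80% power to detect the difference with an alpha error of 5% and two-tailed testing". The two arms are compared over t0 to t3. The visit, contrast or model term that constitutes the difference is not given.
- **Data analyses.** Linear mixed models with repeated measures. No deciding term is named and no rule for several visits is given.
- **Study design, Randomization and trial flow, Control condition.** Controls may use the programme three months after the baseline questionnaire (the Control condition section counts from registration). They are also assessed at t1, t2 and t3.

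**The concern.** The article states an outcome, a hypothesis, an alpha and a sample size, but these do not point to one common test. At least four analyses fit the text: a separate test at each visit, an average over visits, a slope over time, and an omnibus arm-by-time test. They can disagree.

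In this trial the choice also changes what is compared. At t1 and t2 the comparison is programme against no programme. At t3 it is earlier against later access. Success at t1 and t2 with no difference at t3 is therefore a plausible result for a programme that works, and the plan does not say whether that result counts as success.

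Two things are at stake: control of the type I error if the deciding visit is picked after the fact, and dilution of the effect if t3 is pooled with the earlier visits.

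**Working it through.** **1. Does the sample size identify the test?** Inputs: d = 0.2, two-sided 5%, 80% power, 121 per arm.
- Two means at one visit: n = 2(1.960 + 0.842)² / 0.2² = 392.4, so 393 per arm. At 121 per arm, z = 0.2 × √(121/2) = 1.556 and power is 34%. The stated figure is not reproduced.
- The effect that 121 per arm detects with 80% power in such a test is 2.802 × √(2/121) = 0.36.
- Figures near 121 per arm arise only with unstated repeated-measures assumptions. A baseline-adjusted mean of three follow-ups with correlation 0.7 gives 393 × [(1 + 2 × 0.7)/3 − 0.7²] = 393 × 0.31 = 122 per arm. A four-occasion arm-by-time interaction with f = 0.1 and correlation 0.1 gives 247 in total.

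Two different tests land near the same number, so the sample size does not show which was meant. The mismatch with d = 0.2 is a separate matter.

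**2. Type I error.** The plan gives no correlation between visits, so it is assumed.
- One overall test: 5%.
- Any of three unadjusted two-sided 5% tests counts, independent tests: 1 − 0.95³ = 14.3%.
- The same with equal correlation ρ between the test statistics and c = 1.960: 1 − ∫[Φ((c − √ρ·u)/√(1−ρ)) − Φ((−c − √ρ·u)/√(1−ρ))]³ φ(u) du.
- Counting only false findings of benefit, the second Φ term is omitted. A single test then has 2.5%.

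| ρ | any significant visit | benefit only |
|---|---|---|
| 0 | 14.3% | 7.3% |
| 0.5 | 12.5% | 6.3% |
| 0.7 | 10.9% | 5.5% |
| 0.8 | 9.8% | 4.9% |
| 0.9 | 8.4% | 4.2% |

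**3. Timing, in weeks from baseline** (three months taken as 13 weeks).
- t1: 6
- t2: about 6 + 4 = 10
- Control access: about 13
- t3: about 6 + 13 = 19

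A control participant who starts at once has six weeks (19 − 13) before t3, the full length of the programme.

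**4. What pooling t3 can cost.** Illustration with SD 1, 121 per arm complete, equal correlation ρ, effect 0.36 at t1 and t2 and 0 at t3. The effect and ρ are assumptions, 0.36 being the figure from step 1. The SE of the arm difference in the mean of k visits is √[(2/121) × (1 + (k−1)ρ)/k].
- All three visits: effect (0.36 + 0.36 + 0)/3 = 0.24.
  - ρ = 0.5: SE 0.1050, z = 2.29, power 63%.
  - ρ = 0.7: SE 0.1150, z = 2.09, power 55%.
- t1 and t2 only: effect 0.36.
  - ρ = 0.5: SE 0.1113, z = 3.23, power 90%.
  - ρ = 0.7: SE 0.1185, z = 3.04, power 86%.

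These use follow-up means without baseline adjustment. Adjusting for baseline replaces the factor (1 + (k−1)ρ)/k by that factor minus ρ². Power then becomes 82% / 92% for three visits (factors 0.417 / 0.310) and 98% / over 99% for t1–t2 (factors 0.500 / 0.360). The ordering stays and the gap narrows.

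If the effect were 0.36 at all three visits, the three-visit average would be slightly better: z = 0.36/0.1050 = 3.43 (93%) and 0.36/0.1150 = 3.13 (88%).

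**The case against.** The strongest reply is that the text leans towards a single longitudinal comparison. The sample size section speaks of one difference over t0 to t3, there is one primary scale, and a repeated-measures mixed model is planned. Any one overall test from that model has 5% error. A reader might infer that the trial's false-positive risk is about 10% to 12%. The documents do not support that: nowhere do they say that three separate tests will be run or that one significant visit suffices, and the figure also needs a correlation of about 0.6 to 0.8 that they do not give. This part of the objection stands.

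A reader might also infer that an omnibus arm-by-time test would lose much power. With baseline in the model and an effect of 0.36 at every follow-up, that test has 83% / 97% power at ρ = 0.5 / 0.7, against 90% / 99% for the matching t1–t2 change contrast. The loss is modest and is no part of this point.

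The article is condensed, and an analysis plan and a preregistration that are not shown may name the term. That excuses missing model detail. It does not settle which comparison the stated outcome, alpha and sample size refer to, which belongs in the protocol and which the article addresses without resolving.

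Finally, the PPCS looks back six months, so at t1 and t2 most of the recall window precedes randomisation: about 20 and 16 of 26 weeks, against about 7 at t3. This is a real weakness of the earlier visits and has to be weighed in the fix.

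**Conclusion.** The point holds as a gap in the definition of the primary comparison. Three follow-ups share the primary outcome, one alpha and one sample size attach to an unidentified difference, and no deciding model term is given. Mixed results across visits therefore cannot be adjudicated.

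The inflation is conditional. It is about 8% to 14% (about 4% to 7% for false findings of benefit) only if any unadjusted visit may count, with assumed correlation 0.9 to 0. Under one overall test it is 5%.

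The timing of t3 makes this more than missing detail, because pooling it brings into the primary comparison a visit at which controls may already have used the programme. The size of the dilution rests on assumptions about control uptake and the effect at t3. The power figures of 63% / 55% against 90% / 86% illustrate it and do not predict it.

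This should be fixed before analysis. It does not invalidate the design.

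**What to change.** In the Introduction, Sample size calculation, Hypotheses and Data analyses, name one primary test: the baseline-adjusted arm difference in PPCS, averaged over t1 and t2, as a single one-degree-of-freedom contrast from the linear mixed model at two-sided 5%. Report the visit-specific differences and t3 as secondary estimates with 95% confidence intervals and no success claim. Restate the power calculation for the named contrast, with its assumed correlation and effect. State that t3 follows control access, so that those passages and the use of t3 in the primary comparison are reconciled.

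The change is wording only, but it should be made and dated before outcome data are analysed, since recruitment was already under way. It has two costs. The confirmatory claim at t3 is given up. The primary contrast also rests on visits whose six-month recall window overlaps the period before randomisation, which the protocol should acknowledge as a limitation.

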## Methods

### Study design

The web-based (online) self-help program, Hands-off, will be evaluated with a two-armed RCT comparing the efficacy of the (1) intervention condition with the (2) wait-list control condition. Participants assigned to the control condition will access the intervention materials three months after completing the baseline questionnaire set. Participants will be unaware of the hypotheses of the study but will be aware of the assigned condition. Any blinding of study personnel is unwarranted, as they will not be directly involved in the intervention or the assessment. After completing the baseline self-report questionnaire (t_0_), participants will be randomly assigned to one of the two study arms. Further assessments will take place right after the end of the six-week-long intervention (t_1_), at a one-month follow-up (t_2_), and three-month follow-up (t_3_) after the end of the intervention (Fig. 1). The study was preregistered on the Open Science Framework (OSF) Website (https://osf.io/5tqkb/).

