### Randomization and trial flow

After the baseline assessment, randomization will take place at an individual level by an automated, computer-based algorithm on the intervention website. A randomization list will be created in a 1:1 ratio. After the randomization, participants in the intervention condition will receive immediate access to the online intervention, while participants in the control condition will receive access to the intervention three months after the completion of the baseline questionnaire. Participants will know to which group they have been assigned. The intervention condition will last six weeks. Follow-up assessments will be completed online and will take place right after the end of the six-week-long intervention (t_1_), at a one-month follow-up (t_2_), and three-month follow-up (t_3_) (Fig. 1). If the final assessment is not completed, up to two reminders will be sent out 2 and 5 days later.

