#### Other elements

In some exercises (e.g., pros and cons of pornography use), participants will be asked to enter their answers by clicking on checkboxes or entering text freely. This information will be accessible for them anytime in their Profile (“My inputs” section). Entering information during the program would not only result in higher levels of engagement but may also be considered as an effective self-persuasion technique (Aronson, 1999; Sniewski & Farvid, 2019). Moreover, adherence to the treatment will be monitored, and reminders will be sent via e-mails after seven (14, 21, 28) days of non-compliance (i.e., not logging in to the intervention website or not completing the daily diary of pornography use and mood).

### Control condition – Study arm 2

Participants randomized to the wait-list control group will be provided the opportunity to participate in the intervention condition (study arm 1) three months after registration. Participants will also complete the baseline (t_0_) and the follow-up (t_1_, t_2_, and t_3_) assessments.

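### The three-month follow-up (t3) falls six weeks after controls are offered the program, yet it counts in the primary comparison with control as if controls were still waiting

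*Protocol article*

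**What the plan says.** **Control access.** Study design states: "Participants assigned to the control condition will access the intervention materials three months after completing the baseline questionnaire set". Randomization and trial flow repeats this: "participants in the control condition will receive access to the intervention three months after the completion of the baseline questionnaire". The section on the control condition (Study arm 2) counts from a different start, "three months after registration".

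**Visits.** Randomization and trial flow gives the program length: "The intervention condition will last six weeks". Study design puts the later visits "at a one-month follow-up (t_2_), and three-month follow-up (t_3_) after the end of the intervention". The abstract's Methods agrees that the follow-ups run from the end of the intervention.

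**Who is assessed.** For controls: "Participants will also complete the baseline (t_0_) and the follow-up (t_1_, t_2_, and t_3_) assessments".

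**What is compared.** The last paragraph of the Introduction says: "The primary outcome will be the change in the level of PPU between baseline and follow-up assessments". It then lists t1, t2 and t3 and sets the change against a control condition. Sample size calculation likewise compares the two groups over t0 to t3. Data analyses plans intention-to-treat linear mixed models over the repeated measures.

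**PANAS.** Table 3 schedules positive and negative emotions at t0 and t3 only.

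**The concern.** The control-access period and the t3 interval are both three months, but they start at different points. Access is counted from baseline, and t3 from the end of the six-week program. Controls are therefore offered the program before the last visit at which they serve as the comparator. No section delays access until after t3, limits the between-arm comparison to earlier visits, or sets apart control data collected after access.

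At stake is the meaning of one of the three follow-ups in the primary outcome. If the program works and some controls use it, the difference at t3 shrinks even when the intervention arm keeps all of its benefit. Maintenance at three months is what a visit this late is meant to show, and a shrinking difference there would look like a fading effect.

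The problem is sharper for positive and negative emotions, which the Hypotheses section names among the secondary outcomes. Their only follow-up in Table 3 is t3.

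**Working it through.** **1. Timeline.** The article gives no computed figure for this point, so the check is date arithmetic from baseline, with a month of length m.

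- t1 = 6 weeks
- t2 = 6 weeks + m
- control access = 3m
- t3 = 6 weeks + 3m
- t3 − access = (6 weeks + 3m) − 3m = 6 weeks, whatever the value of m

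| Month convention | t1 | t2 | Access | t3 | Access − t2 |
|---|---|---|---|---|---|
| Calendar | wk 6.0 | wk 10.3 | wk 13.0 | wk 19.0 | 2.7 wk |
| 30 days | wk 6.0 | wk 10.3 | wk 12.9 | wk 18.9 | 2.6 wk |
| 4 weeks | wk 6.0 | wk 10.0 | wk 12.0 | wk 18.0 | 2.0 wk |

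t1 and t2 precede access under every convention. Counting from registration can only bring access forward. The article gives no interval between registration and the baseline questionnaire. t2 would be reached only if that interval exceeded 2.0 to 2.7 weeks.

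**2. Illustration of size.** From the article: d = 0.2, 121 per arm, two-sided 5%. (A simple two-group test at d = 0.2 needs 393 per arm for 80% power. That is a separate matter, and 121 is used here only as the planned size.) Assumed, and not in the article: the same effect d at t1, t2 and t3 against untreated controls; an equal correlation r between any two visits; adjustment for baseline; no dropout; and a share u of the effect that controls have gained by t3.

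- Average effect over t1–t3: δ = (d + d + (1 − u)d)/3. This is 0.200 for u = 0, 0.183 for u = 0.25, 0.167 for u = 0.5 and 0.133 for u = 1.
- Variance factor: V = (1 + 2r)/3 − r² for three visits and V = (1 + r)/2 − r² for two.
- Standard error = √(2V/121). Power = Φ(δ/SE − 1.96), the opposite tail being negligible.

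At r = 0.6 with three visits, V = 2.2/3 − 0.36 = 0.373 and SE = 0.0786. For u = 0, 0.200/0.0786 = 2.55, so power is 72%. For u = 1, 0.133/0.0786 = 1.70, so power is 40%. With t1 and t2 only, V = 0.8 − 0.36 = 0.44, SE = 0.0853 and 0.200/0.0853 = 2.35, so power is 65%.

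| Analysis | r = 0.5 | r = 0.6 | r = 0.7 |
|---|---|---|---|
| t1–t3 average, no catch-up | 67% | 72% | 80% |
| t1–t3 average, quarter catch-up | 60% | 65% | 73% |
| t1–t3 average, half catch-up | 52% | 56% | 64% |
| t1–t3 average, full catch-up | 36% | 40% | 46% |
| t1–t2 average | 59% | 65% | 74% |

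**3. Omnibus test.** A 3-degree-of-freedom test of the arm effect at t1, t2 and t3 has noncentrality (121/2)·m′Σ⁻¹m. Here m = (d, d, (1 − u)d), and Σ has 1 − r² on the diagonal and r − r² off it. At r = 0.6, power is 55% with no catch-up, 48% with half and 58% with full. At r = 0.5 it is 50%, 43% and 50%. Catch-up therefore does not lower the power of every test, because a difference that changes over time is itself evidence against the null. Such a result would still not show what happens to the benefit at t3.

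**The case against.** The strongest reply accepts the dates and disputes how much they matter.

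- **Uptake is voluntary.** A reader might infer that t3 compares treated with treated participants. The article does not support that. Controls are only offered the program, the modules are sequential with one suggested per week, and the article itself expects low adherence and high dropout. Only a control who starts at once and keeps pace would finish by t3. This stands, so full catch-up is a worst case and the true attenuation is unknown.
- **Six-month recall.** The PPCS covers the past six months. At t3 (about day 133) only about 42 of some 182 recalled days follow control access, which may soften the effect. At t2 (about day 72), however, about 182 − 72 = 110 days precede baseline, so t1 and t2 have a limitation of their own. Both points stand. Neither restores an untreated comparator at t3.
- **Not every test loses power.** A reader might infer that any arm-by-time test is diluted. Step 3 shows otherwise. The loss applies to an averaged contrast, which the article does not say is planned. Separate contrasts at t1 and t2 are untouched.
- **Multiplicity.** A reader might also infer an inflated false-positive rate from testing three visits at 5% each. The article plans mixed models and does not state three separate tests. The rule for the primary contrast is commonly left to an analysis plan, so this is not part of the point.
- **An analysis plan could settle it.** The access date, visit schedule and primary outcome are all fixed in the article. An analysis plan could remove the conflict only by departing from the primary outcome stated there.

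**Conclusion.** The plan is wrong as written on t3. From its own intervals, controls are offered the program six weeks before t3, yet t3 is counted in the primary comparison with control. What t3 estimates is immediate versus delayed access. If the program works, the bias is toward no difference, and its size depends on control uptake, for which the article gives no figure. The same holds for the only follow-up comparison of positive and negative emotions. The comparisons at t1 and t2 are not affected by control access.

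The timing conclusion needs no assumption beyond the stated intervals. The power figures do: they rest on the assumed correlation, baseline adjustment, constant effect and catch-up share, and they apply to an averaged contrast. Under those assumptions, dropping t3 costs power when controls gain little (72% to 65% at r = 0.6 with no catch-up). It roughly breaks even at a quarter catch-up and gains power beyond that. The case for setting t3 apart is therefore mainly that it answers a different question, and only secondarily that it may cost power.

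**What to change.** Base the confirmatory between-arm comparison on the visits before control access, t1 and t2. Report t3 separately as immediate versus delayed access, together with within-arm maintenance in the intervention arm, and make no claim against untreated controls at that visit. Label the PANAS comparison at t3 in the same way.

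If the sponsor wants a between-arm claim at t3, the control-access time and the t3 schedule must first be reconciled across Study design, Randomization and trial flow, and the control-condition section. In either case, the start of the waiting period (baseline questionnaire or registration) should be stated in one way throughout.

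The main change is to wording. The cost is that no randomised three-month claim against untreated controls can be made under the present timing. Some power is also lost relative to a three-visit average if few controls take up the program.
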